## Abstract

**Aims:**

The main purpose of this study is to develop an indirect screening system for paternal perinatal depression based on the female partner's assessment in the Japanese population. The Japanese version of the Edinburgh Postnatal Depression Scale‐Partner (EPDS‐P) will be used as the indirect screening tool, and its accuracy will be studied in this longitudinal prospective observational study.

**Methods:**

Public health nurses and midwives at the participating community health center are currently inviting couples to participate, and are distributing self‐rating scales to the participants. The primary evaluation scales being used in this study are the Japanese versions of the Center for Epidemiologic Studies Depression Scale (CES‐D) and the Japanese version of the EPDS‐P which evaluates paternal perinatal depression by women. We will evaluate EPDS‐P performance against CES‐D, including accuracy, sensitivity, specificity, and correlations.

**Results and Conclusions:**

Perinatal depression is a mental illness that occurs between pregnancy and postpartum within the 12 months, and it is known to increase the risk of adversely impacting on child development. Men may also experience a psychosocial crisis during their partners' perinatal period. Although it was recently reported that the EPDS‐P can indirectly detect paternal perinatal depression, there is, as yet, insufficient evidence of this because the previous studies had relatively small sample sizes and were limited to cross‐sectional studies in the postpartum period. The development of a screening system for paternal perinatal depression using the EPDS‐P will lead to increased awareness of the disease and provide an opportunity to establish a family‐based support system in Japan.

## INTRODUCTION

1

Perinatal depression is a psychiatric disorder that occurs during pregnancy and within the first year postpartum, and it is known to increase the risk of adverse impacts on child development.^1^, ^2^, ^3^, ^4^ Known causes of maternal perinatal depression include biological, psychological, and social problems, with family support having a strong positive impact on women's mental health.^5^ For this reason, men are generally encouraged to assist women and children during the perinatal period.^6^ It has become clear that men may also experience psychosocial crises and high rates of depression during the perinatal period.^7^ An international meta‐analysis found the prevalence of paternal perinatal depression to be 8.4%.^8^ In addition, paternal perinatal depression is known to increase the risk of suicide in men.^9^ Our previous meta‐analysis found the prevalence of perinatal depression among Japanese men to be approximately 10%, with no statistically significant difference in prevalence between men and women in terms of relative risk.^10^ Risks of maternal and paternal perinatal depression as well as child abuse are reported to correlate with each other.^9^, ^11^ This suggests that supporting the father might ultimately have a positive impact on the mental stability of the mother and on the development of the child.^12^ Therefore, it is necessary to assess the mental state of men as well as of women, and to provide appropriate support during the perinatal period. However, men are less likely to participate in the perinatal support system than are women.

In addition, health care professionals have tended to overlook the fact that men can also experience perinatal depression, and Japan lacks systems for screening and prevention of paternal perinatal depression.^13^ These factors make it difficult to detect paternal perinatal depression in Japanese men.^14^ Furthermore, inadequate knowledge of paternal postpartum depression among health care professionals might be a barrier to appropriate treatment.^15^ For this reason, more attention should be paid to paternal perinatal depression during routine perinatal checkups. In addition, providing information and support for men about paternal perinatal depression using an online screening and support system is also important because it offers the advantage of easy access to information with fewer human and physical constraints^16^, ^17^ but not yet widespread enough in Japan. Therefore, new systems to support men's mental health during the perinatal period are being considered. Unfortunately, a previous Japanese study suggested that the validity of the Japanese versions of the Kessler Psychological Distress scales, K6^18^ and K10,^19^ and the Patient Health Questionnaire‐9 (PHQ‐9)^20^ might be compromised when used by women to assess perinatal depression in their male partners.^21^

For the assessment of perinatal depression, the Edinburgh Postnatal Depression Scale (EPDS), a 10‐item self‐rating scale devised by Cox et al.^22^ is commonly used. The Japanese version of the EPDS has also been validated and widely used.^23^ In recent years, the EDPS‐Partner (EPDS‐P) has been developed to assess perinatal depression based on the EPDS, and studies have indirectly assessed perinatal depression in men through women.^24^ The EPDS‐P can indirectly screen fathers for perinatal depression through maternal reports, even when fathers do not participate in perinatal maternal and child support services or when a coronavirus pandemic makes it difficult for fathers and mothers to access healthcare resources. The EPDS‐P can indirectly assess postpartum depression in men with a sensitivity of 89% and specificity of 59% with a cutoff value of 4/5 in the general population of the United States; thus, it is attracting attention as a useful assessment tool.^24^ However, the EPDS cut‐off value varies across countries and cultures, and studies have yet to examine the validity of the EPDS‐P for perinatal depression in Japanese men. Also, few studies have examined the longitudinal availability of the EPDS‐P from pregnancy to the postpartum period.^24^ We therefore planned this prospective observational study to examine the validity of the Japanese version of the EPDS‐P to indirectly screen paternal perinatal depression in Japanese men for application to real‐world clinical practice. We believe that the development of a screening system for paternal perinatal depression using the EPDS‐P will lead to increased awareness of the disease and provide an opportunity to establish a family‐based support system in Japan.

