#### Instruments

2.2.1

The following screening instruments are being used for data collection:
The Center for Epidemiologic Studies Depression Scale (CES‐D)This scale was developed by the National Institute of Mental Health (NIMH) for epidemiological studies to detect depression in the general population.^25^ The CES‐D is a 20‐item self‐rating questionnaire that assesses symptoms of depression. The cut‐off value is 16 points, and a Japanese version of the CES‐D (CES‐D‐J) has been validated.^26^
The Edinburgh Postnatal Depression Scale (EPDS)The EPDS is a 10‐item self‐rating scale designed by British psychiatrist John Cox to screen for postpartum depression.^22^ The Japanese version of the EPDS was validated in 1996.^23^ Recently, the EPDS has also been shown to be a reliable and valid measure of maternal prenatal depression^27^ and is attracting attention as a rating scale for paternal perinatal depression.^8^ The diagnostic accuracy of the EPDS for postpartum depression in Japanese men has been reported to have a sensitivity of 81.8% and a specificity of 94.1% in the postpartum period, with a cutoff value of 8,^28^ but a similar study is lacking for the prenatal period.The Edinburgh Postnatal Depression Scale‐Partner (EPDS‐P)In regard to the original English‐language versions, the EPDS‐P was developed to assess postpartum depression in women from man’ perspective.^29^ In contrast, the EPDS‐P developed by Fisher et al.^24^ assesses paternal postpartum depression through maternal reporting. The diagnostic accuracy of the EPDS‐P has been reported to have a sensitivity of 89% and a specificity of 59% with a cutoff value of 4/5, but a Japanese version had yet to be developed. Therefore, with the help of [name], the English version of EPDS‐P for paternal depression was translated into Japanese, and back‐translated into English by three native speakers of Japanese and English and validated its Japanese version.The Mother‐to‐Infant Bonding Scale (MIBS)The MIBS is a self‐rating questionnaire that assesses a mother's feelings toward her infant.^30^ The MIBS includes 10 items that assess the mother–child bond.^31^ Each item is rated on a four‐point Likert‐type scale (0–3). The higher the MIBS score, the weaker the mother–child bond. The Japanese version of the MIBS has been previously validated and is commonly used in Japan to assess mother–child bonding.^31^

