### Outcome measures

2.3

The primary outcome will be accuracy of the EPDS‐P in determining paternal perinatal depression in Japanese men. Presence of paternal depression is determined based on the CES‐D, with a CES‐D total score of 16 or higher considered depression.

Then, ROC curves are drawn and AUCs are calculated to examine the discrimination accuracy of the two groups (depression or not) by EPDS‐P. Discriminatory value of ROC curves was interpreted as excellent (AUC 0.9–1), good (0.8–0.89), fair (0.7–0.79), poor (0.6–0.69), or fail/no discriminatory capacity (0.5–0.59).^32^ On the other hand, the point on the ROC curve where “sensitivity + specificity” is maximized is defined as the optimal cut‐off point. The sensitivity and specificity at the cutoff point are calculated, respectively.

The secondary outcome will be whether prenatal EPDS‐P can predict paternal postpartum depression using longitudinal data from pregnancy and the early postpartum period. Furthermore, we will calculate the correlation between the EPDS and CES‐D in men and analyze the performance of the EPDS in identifying paternal perinatal depression.

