### Data analysis plan

2.5

Upon completion of data collection, the database will be locked for statistical analysis. First, we will calculate the screening accuracy of the EPDS‐P, which in this study assesses depressive symptoms in men by women.

Men with a CES‐D score of 16 or higher are defined as the “depressed” group, and those with a CES‐D score of 15 or lower are defined as the “non‐depressed” group. ROC curves are drawn and AUCs are calculated to examine the discrimination accuracy of the two groups by EPDS‐P score. The discriminatory value of the ROC curves is interpreted as follows: excellent (AUC 0.90–1.00), good (0.80–0.89), fair (0.70–0.79), poor (0.60–0.69), or fail/no discriminatory capacity (0.5–0.59).^32^ The point on the ROC curve where sensitivity + specificity is maximized is defined as the optimal cut‐off point, and the sensitivity and specificity at the cut‐off point are calculated separately.

Next, we will determine the absolute value of Spearman's non‐parametric correlation coefficient between the EPDS‐P and CES‐D. We will also set men scoring 16 or higher on the CES‐D as the depressed group,^26^ and then perform a receiver operating characteristic (ROC) curves analysis to calculate optimal cut‐off values and sensitivity and specificity of the EPDS‐P. We also plan to examine the reliability of the EPDS‐P by calculating its Cronbach's alpha. Cronbach's alpha is the most widely used objective measure of reliability. Alpha is an important concept in the evaluation of assessments and questionnaires. Cronbach's alpha is a confidence coefficient that evaluates whether or not the items measure the same concept or object as a whole (internal consistency) when multiple questions are asked about a characteristic, and the sum of the responses is used as the characteristic scale.^33^ If the Cronbach's alpha coefficient for each item is above 0.6, it is considered to have good internal stability, reliability, and acceptable consistency for an exploratory study.^34^

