The cut‐off value of the EPDS‐P in detecting paternal depression will be calculated at two points: in late pregnancy and within 3 months postpartum. The statistical analysis did not include any participant's response having missing values or an inappropriate number of answers to a question item on a rating scale. Then, as a secondary analysis, we would like to stratify depressed and non‐depressed women, analyze the accuracy of the EPDS‐P in identifying paternal perinatal depression in each group, and examine the impact of women's mental status on the accuracy of the EPDS‐P.

In addition, we will examine the absolute value of Spearman's non‐parametric correlation coefficient between the CES‐D and EPDS in men and the accuracy of the EPDS in identifying depression in men. The depression group is defined as those with a CES‐D score of 16 or higher. Based on this, participants are divided into a depression group or a non‐depression group. We will also report the sensitivity and specificity of the cut‐off points for the EPDS in men at the pregnancy and postpartum. The global performance of the EPDS in men will be expressed as area under the ROC curve.

We will also analyze the characteristics of participants who first developed depression after childbirth.

As with maternal depression, paternal postpartum depression might develop during pregnancy, so we will calculate the proportion of cases of paternal postpartum depression that develop throughout the prenatal to postpartum period.

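### EPDS-P sensitivity and specificity are fixed only at a cut-off derived from the study's own data; no estimate at the published 4/5 threshold is pre-specified, so the result will not be like-for-like with 89%/59%

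*Protocol article*

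**What the plan says.** The Introduction (section 1) reports that the EPDS-P identifies depressed fathers after the birth "with a sensitivity of 89% and specificity of 59% with a cutoff value of 4/5 in the general population of the United States". It then gives the reason for a Japanese study: "the EPDS cut‐off value varies across countries and cultures, and studies have yet to examine the validity of the EPDS‐P" in that population. Instruments (2.2.1) repeats the published figures: "sensitivity of 89% and a specificity of 59% with a cutoff value of 4/5, but a Japanese version had yet to be developed".

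Outcome measures (2.3) sets the primary outcome: "The primary outcome will be accuracy of the EPDS‐P in determining paternal perinatal depression in Japanese men", with depression defined as a CES-D score of 16 or more. The threshold rule, in 2.3 and again in the Data analysis plan (2.5), is: "The point on the ROC curve where sensitivity + specificity is maximized is defined as the optimal cut‐off point". Sensitivity and specificity are then calculated at that point. Section 2.5 adds: "The cut‐off value of the EPDS‐P in detecting paternal depression will be calculated at two points", namely late pregnancy and within 3 months postpartum. The analysis that predicts postpartum depression from the pregnancy score uses the same rule. ROC curves by EPDS-P score and AUCs with verbal bands are also planned.

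No part of the article plans an EPDS-P estimate at 4/5.

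**The concern.** A sensitivity–specificity pair belongs to its threshold. Raising the threshold lowers sensitivity and raises specificity, even when the scale behaves identically in two countries. A pair reported at a data-derived threshold therefore cannot be set against 89%/59% unless that threshold happens to be 4/5.

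The derived cut-off has the same problem. With about 54 depressed men, the maximum of sensitivity + specificity moves by a point or two through chance alone. The article also does not say by what rule 4/5 was chosen, so a different selection rule could separate the two cut-offs as well. Because the Introduction prepares the reader for cut-offs that vary between cultures, a Japanese cut-off other than 4/5 could be read as evidence of such a difference when it is not.

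This is distinct from optimism in the derived pair. Correcting that optimism would still leave an estimate at a different threshold.

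**Working it through.** **1. Numbers available (Sample size calculation, 2.4).** The inputs are prevalence 10%, margin 0.025 and 95% confidence. The plan's figure reproduces: n = 1.96² × 0.10 × 0.90 / 0.025² ≈ 553.2, rounded up to 554. The target of 600 pairs at a 90% valid response rate gives 600 × 0.90 = 540 valid pairs: 54 depressed and 486 non-depressed men per time point.

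**2. How often the rule leaves 4/5 when 4/5 is right.** Assumptions, none of them in the documents:
- EPDS-P scores follow truncated negative-binomial distributions on 0–30.
- They are solved so that P(score ≥ 5) is 0.89 in depressed men and 1 − 0.59 = 0.41 in non-depressed men.
- Only the six distributions in which 4/5 truly maximises sensitivity + specificity are kept.

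In 2,000–3,000 simulated studies for each distribution (54 vs 486), the derived cut-off differed from 4/5 in 50–62% at one time point. No figure is given for the two time points together, because the same couples are followed and the correlation between their scores is unknown.

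**3. What a shift in threshold does by itself.** True accuracy in those distributions (ranges run across distributions):

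| Cut-off | Sensitivity | Specificity |
|---|---|---|
| 3/4 | 94–95% | 49–52% |
| 4/5 | 89% | 59% |
| 5/6 | 81–82% | 65–67% |
| 6/7 | 71–74% | 70–74% |

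Moving up one or two points lowers sensitivity by between 89 − 82 = 7 and 89 − 71 = 18 points, with no change in how the scale performs.

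**4. A second model.** Take an equal-variance binormal model calibrated to the same 89%/59%, with score steps of 0.2 or 0.3 SD. The published Youden index is 0.89 + 0.59 − 1 = 0.48 and the implied AUC is about 0.85. The true optimum here is a score of 7 or more, with index about 0.53, so 4/5 is not the optimum. Over 5,000 simulated studies per step size, the rule picks 4/5 in only about 4–6% and overstates the index by about 0.03 on average. The frequency depends heavily on the model. In both models a derived cut-off other than 4/5 is common although accuracy at 4/5 is exactly as published.

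**5. Precision at a fixed 4/5, if 89%/59% held (Wilson 95% intervals).** The interval is [p + z²/2n ± z√(p(1−p)/n + z²/4n²)] / (1 + z²/n).
- Sensitivity: 48/54 = 0.889. Centre (0.8889 + 0.0356)/1.0711 = 0.863, half-width 0.085, giving 78% to 95%.
- Specificity: 287/486 = 0.591. Centre (0.5905 + 0.0040)/1.0079 = 0.590, half-width 0.044, giving 55% to 63%.

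**The case against.** **The article never undertakes to test 4/5.** The objective (1.1) is to develop a screening system for Japan and to study the scale's accuracy. Deriving a local cut-off serves that, and 89%/59% is cited as background. This stands: transfer of 4/5 is part of the motivation and is not a listed objective, so the plan does not contradict itself. An analysis plan that is not shown could also add the row. What remains is that the article does state where accuracy will be reported, for its primary outcome, and that place is the derived cut-off alone.

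**A reader might infer that the study cannot say whether the published accuracy carries over.** The documents do not support that. The planned ROC curve by EPDS-P score passes through the point for a score of 5 or more, so the estimate can be obtained from data already being collected.

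**A reader might also take 89%/59% as the plan's only yardstick.** It is the only published EPDS-P pair cited. The plan also sets AUC bands, and it cites figures for the man's own EPDS ("sensitivity of 81.8% and a specificity of 94.1% in the postpartum period, with a cutoff value of 8").

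**The comparison is itself limited.** The published pair concerns postpartum depression, and its reference standard and sample size are not given here. A difference at 4/5 could come from reference standard, translation or sampling error. This stands and restricts how the comparison may be worded. The interval of 78–95% for sensitivity also contains the 81–82% seen at 5/6, so small shifts will not be resolved.

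**The man's own EPDS.** Instruments gives a postpartum cut-off of 8, "but a similar study is lacking for the prenatal period". Section 2.5 promises accuracy at cut-off points for this scale in pregnancy and postpartum without restricting them to a derived optimum. That is no more than a possible extra row.

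**Conclusion.** The point holds as a gap in pre-specified estimation, with modest consequences and a nearly free remedy. The article fixes EPDS-P sensitivity and specificity only at a threshold chosen from its own data. The reported pair will therefore often not be comparable with the one published EPDS-P pair it cites, and a derived cut-off other than 4/5 is weak evidence that Japan needs its own.

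The size, roughly 50–62% of studies at one time point, rests on assumed score distributions with 4/5 truly optimal and on 54 depressed among 540 valid pairs. It shows direction and rough scale only. It would go too far to say that the design cannot answer the question, that the plan promised a test of 4/5, or that a difference from 89%/59% could be put down to culture.

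**What to change.** In 2.3 and 2.5:

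- Pre-specify sensitivity and specificity with 95% confidence intervals at EPDS-P 4/5 (score of 5 or more) at both time points, beside the derived cut-off.
- Compare only the postpartum figures with 89%/59%. State that the reference standard behind the published figures is not given and that a difference cannot be attributed to culture alone.
- Report the difference in sensitivity + specificity between the derived cut-off and 4/5, with a bootstrap interval that re-selects the cut-off in each resample.
- Do not describe the derived value as a distinct Japanese cut-off on its point estimate alone.
- Optionally, add a row for the man's EPDS at the published cut-off of 8 at both time points.

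The cost is a few sentences, a short bootstrap and a few table rows, with no new data or participants. The downside is that the derived cut-off may prove indistinguishable from 4/5 and would have to be reported so.

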### Objective

1.1

The main purpose of this study is to develop an indirect screening system for paternal perinatal depression based on the female partner's assessment in the Japanese population. The Japanese version of the EPDS‐P will be used as the indirect screening tool, and its accuracy will be studied in this longitudinal prospective observational study. Additionally, we will also investigate whether there is a correlation between depressive symptoms and risk of child maltreatment in women and men in our study participants.

## METHODS AND ANALYSIS

2

### Study design and subjects

2.1

This study is a prospective longitudinal observational study of the participating couples in Towada City, Japan. Research participants are being recruited during perinatal home visits by public health nurses and midwives from a community health center in Towada City, Aomori Prefecture, Japan. All research participants will receive a full explanation of the study and provide written informed consent. The mental status of the participants will be assessed using self‐rating scales. Assessments will be conducted at two points: late in pregnancy and within 3 months postpartum. We will provide potential study participants with information about perinatal depression, regardless of their rating scale scores or consent to participate in the study. We will also explain that support from public health nurses and treatment from physicians will be available. For residents at high risk of perinatal depression such as high EPDS and CES‐D scores, poor childcare support, and extreme economic deprivation, we will develop support through collaboration between health centers and medical institutions.

The target population is the general public of Towada, a city located in the southern part of Aomori Prefecture, Japan, with a population of approximately 60 000. Public health nurses or midwives at the Towada Community Health Center are carrying out the recruitment of research participants, and they have sufficient experience in perinatal maternal and child support, and have received research ethics training beforehand. The explanatory document and questionnaire have been prepared in Japanese, and participants who cannot understand Japanese will be excluded from the study. Participants under 20 years of age will also be excluded from the study because they cannot legally consent to the study.

